### NDII

The NDII is a procedure-specific health-related quality of life (HRQoL) assessment tool. The tool is validated for use in patients who have undergone selective or modified radical neck dissection [20]. Patients will undertake a baseline NDII pre-operatively and at follow-up visit 2 (4–6 weeks). Although the NDII is not validated for use 4–6 weeks after surgery, there is evidence that the NDII score at this early juncture is representative of longer-term HRQoL [23].

### WHQ

The WHQ has been developed and validated for use in the Bluebelle study; a feasibility study of different wound dressing strategies for the prevention of surgical site infection in elective and unplanned abdominal surgery [21]. Currently, the WHQ has not been validated for use in Head and Neck Surgery. Patients recruited to the DEFeND study will complete the WHQ at follow-up visit 2 (4–6 weeks). Blinded clinicians will assess the wound using the Centres for Disease Control and Prevention (CDC) criteria of surgical site infection. It is expected that this data will contribute to the validation process.

### Health economics

The health economic (HE) assessment of using FS will be piloted using the ‘incremental cost-effectiveness ratio’ (ICER). This will calculate the average incremental cost associated with each surgical complication prevented when compared to SOC. This will be calculated using the following equation: ICER = ((overall cost of FS arm—overall cost of SOC arm)/(no. of complications in FS arm—no. of complications in SOC arm)).

The variation in costs between the treatment arms will be calculated individually for each patient based on their time in the operating theatre (including returns to theatre), their length of stay within each ward type, their number of hospital visits in the immediate post-operative period (both planned and unplanned), and the cost of materials (including those required to administer FS).

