### Outcomes

The proposed outcome measures for this study can be divided into those that are specific to the pilot study and those informing any future phase III trial seeking to determine the effectiveness of FS in neck dissection. As this is a pilot study, formal assessment of efficacy, cost or safety across treatment arms will not be made.

The outcomes for the pilot study include the following:
Proportion of eligible patients recruited to the study, calculated as the screened to randomisation rate.Reasons for failure to screen potentially eligible patients.Recruitment rate measured as the number of patients randomised each month.Reasons for failure to randomise.Reasons for failure to reveal allocation at a specific time point during surgery.Fidelity of the blinding process (both patients and outcome assessors) as detected by blinding indices.Accuracy of data recording, summarised by the number of key data items with missing/incomplete data entries.Number of patients lost to follow-up.Protocol adherence, measured by the number of major/minor protocol deviations observed through the study.Determining the minimal clinically important difference (MCID) in clinical endpoints by questioning recruited patients and recruiting clinicians.

The clinical outcomes to inform a future phase III trial include the following:
Clavien-Dindo classification of surgical complications [19].Twice daily wound drainage volume (ml).Time (hours) for daily wound drainage volume to reach < 1.25 ml/h.Time (hours) to drain removal (as dictated by drainage volume).Total wound drainage volume (ml).Time (hours) to be declared medically fit for hospital discharge and time (hours) to actual hospital discharge.Incremental cost-effectiveness ratio.

Patients reported outcomes to inform the future phase III trial include the following:
Neck Dissection Impairment Index (NDII). This is a procedure-specific patient-reported outcome measure [20].Daily patient-reported pain score using visual analogue scale (VAS).Wound Healing Questionnaire (WHQ). This is a questionnaire currently in the process of validation to assess wound healing after surgery [21].

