### Sample size

As this is a pilot study, no formal power/sample size calculation based on clinical data is given. For this study, the two main outcomes of interest are to determine accurate estimates of the rate of recruitment (being the number of patients recruited relative to the number eligible) and to collect sufficient clinical data to accurately estimate a sample size for a future study. It is estimated that over the study period, approximately 50 patients will be recruited at rate of 30%. Based on this, 50 patients (25 in each arm) will produce a standard error of approximately 6.5% and a 95% confidence interval of approximately (17–43%) will be obtained. With respect to surgical complication rate, being the clinical outcome of current greatest interest, even if a response rate of 50% is observed, then a 95% confidence interval of (0.36, 0.64) will be observed which provides sufficient precision for a future sample size.

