### Allocation

Randomisation lists will be computer-generated by the statistician prior to the recruitment of the first patient. Patients will be randomised using a 1:1 ratio. Lists will be produced based on the principle of randomly permuted blocks with random block sizes of 2 and 4. Patients will only be stratified according to the hospital in which they receive their treatment.

The process of randomisation will be undertaken pre-operatively using the “Treatment Allocation RanDomIsation System” (TARDIS) software version 3.8. This software has been developed by the LCTU. The allocation will be concealed to everyone including the person performing the randomisation. Once randomisation has been performed, the surgeon caring for the patient will receive an automated email which contains a link to reveal the allocation. Once the patient has undergone their neck dissection immediately prior to the point of wound closure, the surgeon will open the link and login to TARDIS to reveal the allocation. The exact time and date this occurs will be recorded and cross-referenced against the start and finish times of surgery as a quality assurance step to minimise performance bias. The randomisation process can be performed either centrally or at the site once the eligibility criteria have been entered and signed off by the Principal Investigator.

As part of the blinding strategy, any clinicians who will be assessing study outcomes must leave theatre prior to the revealing of treatment allocation. They must not return until the theatre has been cleared of any evidence of FS usage. The surgeon administering the FS will not be allowed to assess study outcomes for the patient and must delegate this responsibility to a suitable colleague.

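### The printed ICER equation contradicts its own definition: its denominator is the negative of complications prevented, and it uses arm totals where per-patient means are needed

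*Protocol article*

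**What the plan says.** The Health economics section of the protocol article states the intended quantity in words: "This will calculate the average incremental cost associated with each surgical complication prevented when compared to SOC". It then prints the equation. The numerator is "overall cost of FS arm—overall cost of SOC arm" and the denominator is "no. of complications in FS arm—no. of complications in SOC arm". Both are totals over an arm. The section gives no sign convention and no division by the number of patients, although costs "will be calculated individually for each patient based on their time in the operating theatre" and other items of resource use.

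Three other sections matter. Sample size plans 50 patients, 25 per arm. Allocation stratifies by hospital only, using "randomly permuted blocks with random block sizes of 2 and 4", and Trial design names two hospitals. Outcomes lists the ICER among the clinical outcomes meant to inform a phase III trial, and also says that "formal assessment of efficacy, cost or safety across treatment arms will not be made".

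**The concern.** The words and the equation describe quantities of opposite sign. Complications prevented by FS are the SOC count minus the FS count; the equation uses FS minus SOC. Putting both differences in the same arm order is the usual form when the effect is a benefit. Here the effect is a count of harms and the text speaks of harms prevented, so the order has to be reversed.

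The totals are a separate fault. If one arm has more patients, the extra patients' costs and complications enter the two differences as if the sealant had caused them.

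At stake is whether the ratio carried forward to the phase III economic design means what the text says it means. Someone applying the equation literally and labelling the result by the definition would report a figure of the wrong sign and, with unequal arms, of the wrong size.

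**Working it through.** The protocol prints no ICER value, so there is no figure to reproduce. The check is algebra plus a worked example.

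**Inputs.** From the protocol: the definition and the equation (Health economics), 25 per arm (Sample size), blocks of 2 and 4 stratified by hospital (Allocation), two hospitals (Trial design). Assumed for illustration only: mean cost 5,000 per SOC patient, 5,300 or 4,700 per FS patient; 0.4 complications per SOC patient and 0.2 per FS patient.

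**Formulas.** Let C be total cost, E total complications and n patients in an arm.

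- As printed: (C_FS − C_SOC) / (E_FS − E_SOC)
- As defined, per patient: (C_FS/n_FS − C_SOC/n_SOC) / (E_SOC/n_SOC − E_FS/n_FS)

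With n_FS = n_SOC the sample size cancels and the printed value is exactly −1 times the defined value.

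**Step 1: sign, equal arms (25/25).** The cost difference is 25 × 300 = 7,500 in either direction and the complication counts are 5 and 10.

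| Case | As printed | As defined |
|---|---|---|
| FS costlier, fewer complications | 7,500 / (5 − 10) = −1,500 | 300 / 0.2 = +1,500 |
| FS cheaper, fewer complications | −7,500 / (5 − 10) = +1,500 | −300 / 0.2 = −1,500 |
| FS costlier, more complications | 7,500 / (10 − 5) = +1,500 | 300 / (−0.2) = −1,500 |
| FS cheaper, more complications | −7,500 / (10 − 5) = −1,500 | −300 / (−0.2) = +1,500 |

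The sign is reversed in all four cases, whatever costs are assumed.

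**Step 2: totals, unequal arms.** Take the costlier, effective sealant, whose defined value is +1,500 at any arm sizes.

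- 26 FS / 24 SOC: costs 26 × 5,300 − 24 × 5,000 = 17,800; complications 5.2 − 9.6 = −4.4; printed value −4,045.
- 24 FS / 26 SOC: costs 24 × 5,300 − 26 × 5,000 = −2,800; complications 4.8 − 10.4 = −5.6; printed value +500.

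Reversing the denominator while keeping totals would give +4,045 and −500, so correcting the order alone does not cure this fault.

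With no true difference at all (5,000 per patient and 0.2 complications per patient in both arms), a 26/24 split gives 10,000 / 0.4 = 25,000.

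**Step 3: how likely is 26 v 24?** Assume block sizes 2 and 4 are equally likely and 50 patients are split over two hospitals.

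- Both hospitals recruit an odd number: each is out of balance by exactly one patient, so the overall split is 26 v 24 with probability 1/2.
- Both recruit an even number: a hospital is halfway through a block of 4 with probability of about 1/3, and the first two allocations in that block match with probability 1/3. An imbalance of 2 therefore occurs at a given hospital with probability of about 1/9. Exactly one of the two hospitals is out of balance with probability 2 × (1/9) × (8/9) ≈ 0.20.

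Averaging the two cases gives about 0.35. Simulation with 10 to 40 patients at one hospital gives about 34% for 26 v 24 in either direction, about 65% for 25 v 25 and about 0.3% for 27 v 23.

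**The case against.** The strongest reply is about consequence. The protocol calls the economic assessment a pilot, rules out a formal assessment of cost across arms and confines the analysis to descriptive statistics and informal comparisons. The section on progression to phase III lists recruitment rate, safety, sample size estimation and equipoise as examples of what the decision will rest on, and does not mention cost-effectiveness. Per-patient costs and complications are collected, so the right ratio can be recovered at reporting. All of this stands, and it lowers the severity. It does not make the equation right: the equation is printed in full, so this is a misstated rule and not a detail left to a longer document.

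It is also fair to say that totals cancel at the planned 25 per arm and that 27 v 23 is rare. Both stand, which is why the working rests on 26 v 24.

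Three stronger readings are tempting, and the document supports none of them.

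- A reader might infer that the pilot will reach a wrong health-economic conclusion. No stated decision turns on the ICER, and the protocol gives no rule for reading a negative value as a saving.
- A reader might infer that forming a ratio from 25 per arm is itself an error. With assumed risks of 20% (SOC) v 10% (FS) and at most one complication per patient, counts tie with probability 9.8% and FS has more complications with probability 11.2%. Only the tie leaves the ratio undefined; more complications on FS is an interpretable result. This belongs to any ICER in a small sample, and the corrected formula shares it.
- A reader might count the lack of bootstrap intervals or a cost-effectiveness plane as a fault. An article commonly leaves such detail to an analysis plan, and Statistical methods already promises nominal 95% confidence intervals for all results.

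**Conclusion.** The point holds as a correction of one formula that should be made. The sign contradiction is exact for equal arms and needs no assumption about costs or risks. The arm-totals fault is real but conditional: it needs unequal arms, or unequal numbers with data. A 26 v 24 split has a probability of about one third if block sizes are equally likely. The size of the distortion (−4,045 or +500 against a defined value of +1,500) depends on the assumed costs and complication rates; the mechanism does not. Because the ICER is a piloted outcome with no stated progression decision attached, the error threatens the meaning of one descriptive figure passed to phase III planning. It does not threaten the pilot's main findings.

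**What to change.** Replace the printed equation with:

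ICER = (mean cost per FS patient − mean cost per SOC patient) / (mean complications per SOC patient − mean complications per FS patient)

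Add one sentence saying that the cost difference and the complication difference will be reported separately beside the ratio. This is needed even after the correction, because a negative ratio can mean cheaper with fewer complications or costlier with more.

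The cost is one formula and one sentence in the protocol or analysis plan. It needs no new data, no change to the design and no extra patients, because costs are already to be worked out for each patient and complications recorded at every encounter after surgery. It should be done before any ICER is computed.

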### Sample size

As this is a pilot study, no formal power/sample size calculation based on clinical data is given. For this study, the two main outcomes of interest are to determine accurate estimates of the rate of recruitment (being the number of patients recruited relative to the number eligible) and to collect sufficient clinical data to accurately estimate a sample size for a future study. It is estimated that over the study period, approximately 50 patients will be recruited at rate of 30%. Based on this, 50 patients (25 in each arm) will produce a standard error of approximately 6.5% and a 95% confidence interval of approximately (17–43%) will be obtained. With respect to surgical complication rate, being the clinical outcome of current greatest interest, even if a response rate of 50% is observed, then a 95% confidence interval of (0.36, 0.64) will be observed which provides sufficient precision for a future sample size.

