### Objectives

The key objectives of this randomised external pilot study are to assess the following points:
Whether patients can be recruited and retained at a rate of approximately 4 patients per month across the 2 centres.Determining the effectiveness of the blinding strategy using blinding indices.Ensuring the administrative processes of randomisation, allocation concealment and data management work well within the study.Assess adherence to the conditions of the protocol.Provide evidence to inform the sample size calculation for the future phase III multicentre randomised trial

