### Statistical methods

The primary analysis will be carried out on the full data set and will be based on the intention to treat principle, retaining patients in their initially randomised groups irrespective of any protocol violations.

Missing data are expected to be limited, and final analyses are planned to be carried out on a complete case basis. If substantial missing data (> 10%) are observed in either a study outcome or key prognostic covariate, then multiple imputation using chained equations will be applied.

There are no formal comparisons of treatment groups, and therefore, no levels of significance against which hypotheses will be tested. As a guide however, all results will be reported using nominal 95% confidence intervals.

As this is an external pilot study, all data analyses shall take the form of descriptive statistics. Continuous data shall be summarised as medians with associated inter-quartile ranges and categorical data shall be summarised as frequencies of counts and associated percentages.

In terms of clinical outcomes, aside from descriptive statistics, informal comparisons between allocated groups will be made using the difference in means for continuous covariates and differences in rates for categorical covariates.

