## Trial status

Recruitment started on November 06, 2018, and is on target to achieve at the pre-specified sample size in the scheduled 12 months. The interventions appear to be acceptable to potential participants, and approximately 50% of those who have been approached to take part have given written consent. The protocol being used is version 2.0 dated June 27, 2018.

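### The precision stated for the recruitment proportion uses the 50 recruited patients as the denominator, although the rate is defined relative to eligible patients; the plan's own assumptions imply an SE near 3.5%, not 6.5%

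*Protocol article*

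**What the plan says.** The Sample size section names two main outcomes of interest. One is the "rate of recruitment (being the number of patients recruited relative to the number eligible"; the other is the clinical data needed to size a future trial. For the first it expects that "approximately 50 patients will be recruited at rate of 30" per cent, and concludes that "50 patients (25 in each arm) will produce a standard error of approximately 6.5% and a 95% confidence interval of approximately (17–43" (per cent). For the surgical complication rate it adds that "even if a response rate of 50% is observed, then a 95% confidence interval of (0.36, 0.64) will be observed".

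The Outcomes section lists the same recruitment measure as "Proportion of eligible patients recruited to the study, calculated as the screened to randomisation rate". The number of eligible or screened patients expected over the study period is not given in the article.

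**The concern.** A proportion defined as recruited over eligible has eligible patients as its binomial denominator. The 50 patients in the precision statement are randomised patients, since they are split 25 per arm, so they are the numerator of that proportion. Attaching n = 50 to a proportion of 30% would describe 15 patients recruited out of 50 eligible, which contradicts the expectation of 50 recruited.

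What is at stake is the accuracy of the precision statement for one of the two main outcomes, and so one of the two arguments given for the number 50. A reader who takes the figure at face value will think the pilot estimates the recruitment proportion much less precisely than it should. The number of eligible patients that must be found to recruit 50 at 30% also stays hidden.

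**Working it through.** **Inputs**

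- Rate = recruited / eligible (Sample size; the Outcomes section also speaks of the proportion of eligible patients).
- Recruited: 50, as 25 per arm (Sample size).
- Expected rate: p = 0.30 (Sample size).
- Confidence level: 95%, from the Statistical methods section ("all results will be reported using nominal 95% confidence intervals").
- Stated result: SE about 6.5%, 95% CI about 17% to 43%.

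**Step 1: reproduce the stated figure.** For a single proportion, SE = sqrt(p(1 − p)/n) and CI = p ± 1.96 × SE. With p = 0.30 and n = 50:

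- SE = sqrt(0.21/50) = 0.0648, or 6.48%.
- CI = 0.300 ± 0.127 = 17.3% to 42.7%.

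This matches the article. Solving backwards, n = 0.21/0.065² = 49.7, so a denominator of 50 was used.

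**Step 2: check whether 50 could be the number eligible.** If it were, 0.30 × 50 = 15 patients would be recruited. That does not fit 25 per arm. It also does not fit the Objectives section ("Whether patients can be recruited and retained at a rate of approximately 4 patients per month across the 2 centres") combined with the Trial status section ("on target to achieve at the pre-specified sample size in the scheduled 12 months"): 4 × 12 = 48, close to 50. So 50 is the number recruited.

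**Step 3: recompute with the denominator that the definition requires.** Eligible = 50/0.30 = 166.7, about 167.

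- SE = sqrt(0.21/166.7) = 0.0355, about 3.5%.
- CI = 0.300 ± 0.070 = 23.0% to 37.0%.
- Ratio of stated to implied SE: 6.48/3.55 = 1.83, which equals sqrt(166.7/50).
- Interval width: about 25 points with n = 50, about 14 points with n = 167.

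**Step 4: check that the choice of method does not explain the gap.**

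| Method, 50 recruited of about 167 eligible | Result |
|---|---|
| Wald | SE 3.5%, CI 23.0% to 37.0% |
| Wilson, 50/167 | CI 23.5% to 37.3% |
| Clopper–Pearson, 50/167 | CI 23.1% to 37.5% |
| Recruiting until 50 are reached: SE = p × sqrt((1 − p)/50) | SE = 0.30 × sqrt(0.70/50) = 3.5% |

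With 48 recruited instead of 50, eligible = 160, SE = 3.6% and CI = 22.9% to 37.1%. None of these variants comes near 6.5% or 17–43%.

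**Step 5: check the companion interval.** For the complication rate the denominator is the randomised patients, so n = 50 is right: SE = sqrt(0.25/50) = 7.07%, CI 36.1% to 63.9%. This agrees with the printed (0.36, 0.64). One possible explanation of the slip is that the same n was carried over to a proportion with a different denominator.

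**The case against.** The strongest reply is that the error does no damage. It understates the precision, so the design delivers more than it promises. The article says that no formal sample size calculation is given. The complication-rate interval, which is the other support for 50, stands. The Progression to phase III trial section sets no threshold on this interval; recruitment rate is one of several variables that the steering committee will weigh. All of this is correct, and it limits the point to a correction of one sentence.

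A second reply is that 167 appears nowhere in the article. That also stands: it follows from exactly 50 recruited at exactly 30%, and it should be labelled as implied by the planning assumptions. There is a further ambiguity, because the Outcomes section calculates the proportion of eligible patients as a screened to randomisation rate. If more patients are screened than are eligible, the two denominators differ, and so do the rates.

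Neither reply rescues the printed figures. A factor of 1.8 is not rounding. Nor is this a detail left to a fuller document: the stated precision contradicts the definition and inputs given beside it.

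A reader might go further and infer that the final analysis will also divide by 50 and report too wide an interval for planning phase III. The article does not support this. The Sample size and Outcomes sections point to eligible or screened patients, the Recruitment section provides a screening log that can supply them, and dividing the 50 recruits by 50 would return 100%.

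**Conclusion.** The point holds as an internal inconsistency in the Sample size section. The arithmetic is right for n = 50, but n = 50 is the wrong denominator for the rate as defined. The planning assumptions imply an SE of about 3.5% and a 95% CI of about 23% to 37%, so the stated SE and interval are about 1.8 times too large. This rests on 50 recruited, a rate of 30%, and a denominator of eligible patients.

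It would be tempting to conclude that the sample size is poorly justified or too small. The documents do not support that: the corrected precision is better than stated, and the target of 50, the complication-rate interval and the design are unchanged. Nor is a particular interval method needed, since Wald, Wilson and exact limits differ by about half a percentage point here.

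**What to change.** Replace the precision statement with one along these lines: recruiting 50 patients at a rate of 30% implies about 167 eligible patients, giving a standard error of about 3.5% and a 95% confidence interval of about 23–37%. Mark the 167 as implied by the planning assumptions.

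In the same edit, say whether the denominator of the recruitment proportion is eligible or screened patients, and use the same term in the Sample size and Outcomes sections. If it is screened patients, confirm that the 30% refers to that group.

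The cost is one restated sentence and one clarified definition. It needs no extra patients, and the complication-rate sentence needs no change on this ground.

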## Introduction

### Background and rationale

Complications after major surgery are a significant cause of morbidity and mortality and have been shown to have a negative impact on long-term quality of life and psychosocial well-being [1, 2]. In surgical oncology, complications can also delay adjuvant treatment (e.g. radiotherapy) which is known to adversely affect survival [3]. Following resection of the primary tumour, neck dissection is the most commonly performed ‘major operation’ in Head and Neck Surgical Oncology. Hospital Episode Statistics (HES) suggest that approximately 1500 neck dissections are performed within the National Health Service (NHS) in England annually [4]. Significant surgical complications occur in approximately 10–20% of patients undergoing neck dissection [5, 6]. Such risks increase to 40% in patients who have had previous chemo-radiotherapy to the area or when operating on higher risk patients of increasing age, with multiple co-morbidities and/or polypharmacy [7, 8]. Common surgical complications include haematoma formation, surgical site infection, wound breakdown/dehiscence and fistula formation. Management of these complications is frequently painful, invasive and may involve return(s) to theatre. This inevitably delays recovery, which in turn may result in prolonged hospital stay and immobility; both of which are known risk factors for additional complications such as lower respiratory tract infections and venous thromboembolism.

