## Methods/design

### Trial design

This is a randomised external pilot trial set within two UK hospitals offering tertiary head and neck surgery services (Aintree University Hospital NHS Foundation Trust & Queen Victoria Hospital NHS Foundation Trust). Both institutions serve a large population with a mix of both urban and rural communities. Aintree University Hospital treats a population that includes the most deprived 10% of the UK [16]. The target population for this study is patients that are due to undergo lateral neck dissection as part of their treatment for Head & Neck Cancer.

The study design that is being piloted is that of a two-arm, parallel group, superiority trial with block randomisation in a 1:1 allocation ratio. The interventional arm will constitute the application of FS (Artiss, Baxter Healthcare Ltd.) to the surgical wound in addition to standard of care (SOC), and the control arm will constitute SOC alone. For the purposes of this study, SOC constitutes the surgeon performing the neck dissection as they normally would and establishing complete haemostasis. Patients in both arms will have a single surgical drain placed and the wound closed with resorbable sutures across the platysma layer and metal clips to close the skin. The use of FS or any other adjunct to haemostasis in neck dissection is not a common place within the UK. For this reason, the selection of SOC as the comparator is justified. The Consolidated Standards of Reporting Trials (CONSORT) diagram is shown in Fig. 1.

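### The complication-rate interval said to be precise enough to size phase III pools both arms without saying so; the standard-of-care rate rests on 25 patients and its interval is 41% wider at the same rate

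*Protocol article*

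**What the plan says.** The Objectives section of the protocol article lists, among the aims of the pilot, "Provide evidence to inform the sample size calculation for the future phase III multicentre randomised trial". The Sample size section makes this one of the two main outcomes of interest and gives the split by arm: "50 patients (25 in each arm) will produce a standard error of approximately 6.5" per cent, where the standard error refers to the recruitment rate. It then turns to the surgical complication rate, "being the clinical outcome of current greatest interest, even if a response rate of 50% is observed", and concludes: "then a 95% confidence interval of (0.36, 0.64) will be observed which provides sufficient precision for a future sample size". It does not say which patients the interval covers, and it gives no criterion for how precise is precise enough.

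The design being piloted (Trial design) is a "two-arm, parallel group, superiority trial with block randomisation in a 1:1 allocation ratio", comparing fibrin sealant (FS) plus SOC with SOC alone. For background rates, Background and rationale states "Significant surgical complications occur in approximately 10–20% of patients undergoing neck dissection" and adds "Such risks increase to 40% in patients who have had previous chemo-radiotherapy to the area", among other high-risk groups. Under Outcomes, the minimal clinically important difference is to be obtained by questioning patients and clinicians. Statistical methods says "all results will be reported using nominal 95% confidence intervals".

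**The concern.** A 1:1 superiority trial with a binary endpoint is normally sized from two inputs: the event rate under control and the difference worth detecting. The protocol plans to elicit the difference from patients and clinicians, so the main number the pilot's complication data must supply is the SOC event rate. Only half of the 50 patients inform it. An interval based on all 50 describes a mixture of the two arms, which coincides with the SOC rate only if FS has no effect.

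The reassurance offered is that even the worst case gives about plus or minus 14 percentage points. A reader planning phase III could take that as the uncertainty in the control rate. The Progression section lists sample size estimation among the grounds for going on to phase III, so the statement bears on a decision.

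**Working it through.** **Inputs.** 50 patients, 25 per arm, and an observed rate of 50% (Sample size); two-sided 95% intervals (Statistical methods); 1:1 superiority design (Trial design); background rates of 10–20%, rising to 40% in high-risk patients (Background and rationale). The documents give no phase III effect size or power, so those used in step 5 are assumptions.

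**1. Reproduce the printed interval.** Wald: p ± 1.96 × √(p(1−p)/n).
- n = 50, p = 0.5: 1.96 × √(0.25/50) = 0.139, giving 0.361 to 0.639. This is the printed (0.36, 0.64).
- n = 25, p = 0.5: 1.96 × √(0.25/25) = 0.196, giving 0.304 to 0.696. This does not match.

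The printed interval therefore uses both arms together.

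**2. Width of the single-arm interval.** At any given rate the ratio of half-widths is √(50/25) = 1.41, so the SOC-arm interval is 41% wider.

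**3. Wald half-widths across plausible rates.**

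| Rate | Both arms, n = 50 | SOC arm, n = 25 |
|---|---|---|
| 10% | 0.083 | 0.118 |
| 20% | 0.111 | 0.157 |
| 40% | 0.136 | 0.192 |
| 50% | 0.139 | 0.196 |

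**4. Wilson intervals for the SOC arm.** Centre (p + z²/2n)/(1 + z²/n); half-width z√(p(1−p)/n + z²/4n²)/(1 + z²/n); z = 1.96, n = 25.
- 5/25: centre (0.2 + 0.0768)/1.1537 = 0.240, half-width 0.151, giving 0.089 to 0.391.
- 10/25: centre (0.4 + 0.0768)/1.1537 = 0.413, half-width 0.179, giving 0.234 to 0.593.

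**5. What this does to a phase III calculation (illustration only).** Patients per arm = [1.96√(2p̄(1−p̄)) + 0.842√(p₁(1−p₁) + p₂(1−p₂))]² / (p₁−p₂)², where p₁ is the control rate and p̄ is the mean of p₁ and p₂. Assumed: 80% power, two-sided 5%.
- Halving of risk (p₂ = p₁/2), printed pooled interval 0.361 to 0.639: 94 down to 38 per arm, a 2.5-fold range.
- Halving, SOC-arm interval at 50%, 0.304 to 0.696: 119 down to 32, 3.7-fold.
- Halving, SOC-arm interval at 5/25, 0.089 to 0.391: about 495 down to 84, 5.9-fold.
- Relative risk 0.67 instead, same 5/25 interval: 1,257 down to 206, 6.1-fold.

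**6. Pooled rate against SOC rate.** With relative risk R, the pooled rate is p₁(1 + R)/2. With an assumed R of 0.5, a pooled 20% corresponds to an SOC rate of 0.20/0.75 = 26.7%. If FS works, the pooled rate lies below the SOC rate.

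**The case against.** Much can be said for the protocol, and most of it stands.

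- **A reader might infer a miscalculation.** There is none. The interval is right for 50 patients. What is at fault is the missing label and the conclusion drawn from it.
- **A reader might infer that 50% is an irrelevant rate**, because the background gives 10–20%. The documents do not support that. The sentence presents 50% as a limiting case, and it is the conventional choice because it gives the largest absolute width. The 10–20% refers to significant complications, whereas the pilot records every Clavien-Dindo grade. No any-grade rate is given that would rule out 50%.
- **A reader might infer that the SOC arm is far less precise than stated in all circumstances.** In absolute terms it is not. At 10–20% the SOC-arm half-width is 0.118 to 0.157, close to the printed 0.139. The loss there is relative to the rate, which matters most if phase III targets a relative reduction.
- **The size of the effect on phase III depends on the assumed target.** With an assumed 10-point absolute reduction and the same formula, the printed interval gives 336 per arm at its lower limit and 379 at its upper, with a peak of 392 for 55% against 45%. The interval 0.304 to 0.696 gives 297 and 358, with the same peak. In the 50% scenario the arm-level correction then changes little. At lower rates it still matters: an assumed 8-point reduction over 0.089 to 0.391 gives about 113 to 558 per arm, roughly 5-fold.
- **A reader might infer that phase III will be oversized because the pooled rate will stand in for the control rate.** The protocol does not state that step. A pooled rate can also be converted to arm rates once an effect is assumed, and Statistical methods plans between-arm differences in rates, so arm-level rates will be available.
- **This is a pilot.** It needs no power calculation, and phase III design is left to the Trial Steering Committee after closure.

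What remains is an affirmative statement that the precision is adequate, with no criterion, resting on an unlabelled pooled interval, for one of the two main outcomes of interest.

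**Conclusion.** The point holds as a precision claim that the design does not support; it is not an arithmetic error. The printed interval describes 50 patients in two arms, while the SOC rate that sizes a superiority trial rests on 25 and has an interval 41% wider at any given rate: 0.30 to 0.70 instead of 0.36 to 0.64 at 50%. That comparison follows directly from the protocol's own figures.

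The range of about 495 to 84 per arm rests on an assumed halving of risk, 80% power, two-sided 5% and 5 events in 25. It shows why adequacy cannot be taken as given, but it does not predict the size of phase III.

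The matter is worth correcting but is not critical. No pilot analysis, patient number or treatment comparison changes.

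**What to change.** In the Sample size section:

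1. Label (0.36, 0.64) as the overall interval, both arms combined, n = 50.
2. Add the SOC-arm interval (n = 25) over rates of about 10% to 50%: for example 0.30 to 0.70 at 50% (Wald), and 0.23 to 0.59 at 10/25 and 0.09 to 0.39 at 5/25 (Wilson).
3. Delete the statement that the precision is adequate, or qualify it by saying what it would have to be adequate for.
4. State that phase III sizing will use the SOC-arm rate, with the required number shown across its confidence interval and beside the published 10–20% and 40% rates. Where the two are compared, use the same definition of complication, since the published figures are for significant complications only.

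The cost is a few sentences and a less favourable stated precision. No additional patients or data are needed.
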